### Trial design and registration

This is a 1-year feasibility cluster RCT recruiting from primary care. Ten GP practices from East and West Leicestershire and Leicester City clinical commissioning groups (CCG) will be cluster randomised to a structured diagnostic pathway or usual care. The intervention practices will follow a structured diagnostic pathway to include early investigations. Usual care will continue without any intervention.

The University of Leicester will act as study sponsor and the trial has been registered on the ISRCTN website.

### Patient and public involvement

Prior to the trial design an engagement event was held with clinicians and patients from relevant services, including GPs, community and hospital clinicians with cardiorespiratory background and patients with experience of chronic breathlessness to discuss the optimal breathlessness pathway using Listening into Action.^24^ The structured pathway to be used in the trial was the output from this engagement, the NICE guidance and the Breathlessness IMPRESS Tips for Clinicians guidance.^12 14^

The National Institute for Health Research Biomedical Research Centre patient and public involvement (PPI) groups were also consulted about the study design including the duration of the research visits, patient facing information and questionnaire packs. They provided feedback on the type and ordering of the questionnaires and ways to reduce burden to patients. The wording for the electronic template to aid recruitment was developed by members of the PPI group. The trial management and steering groups will have patient members. The study team aim to feed back to all local PPI partners with results from this trial.

### Participants

#### Eligibility criteria for patients

Patients will be eligible if they are over 40 years old, experienced breathlessness for over 2 months and are within their first two presentations to primary care with symptoms of breathlessness. Exclusion criteria are an existing diagnosis for their current symptom of breathlessness, an estimated prognosis of less than 1 year or if the patient requires immediate hospitalisation for their symptoms.

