**Methods and analysis:**

Ten general practitioner (GP) practices across Leicester and Leicestershire will be cluster randomised to either a structured diagnostic pathway (intervention) or usual care. The structured diagnostic pathway includes a panel of investigations within 1 month. Usual care will proceed with patient care as per normal practice. Eligibility criteria include patients presenting with chronic breathlessness for the first time, who are over 40 years old and without a pre-existing diagnosis for their symptoms. An electronic template triggered at the point of consultation with the GP will aid opportunistic recruitment in primary care. The primary outcome for this feasibility study is recruitment rate. Secondary outcome measures, including time to diagnosis, will be collected to help inform outcomes for the future trial and to assess the impact of an earlier diagnosis. These will include symptoms, health-related quality of life, exercise capacity, measures of frailty, physical activity and healthcare utilisation. The study will include nested qualitative interviews with patients and healthcare staff to understand the feasibility outcomes, explore what is ‘usual care’ and the study experience.

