#### Eligibility criteria for GP practices

GP practices will be approached to take part in this study if they serve a patient population over 10 000. Practices that are research active, as identified by the local Clinical Research Network research scheme, will be approached. The practices will be visited by the study team to discuss taking part in the study and engage with the practice teams.

The GP practices will be randomised 1:1 and stratified by CCG using Statarand,^25^ a Stata randomisation module (Boston College Department of Economics).

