#### Recruitment

Patients will be recruited over 1 year. Patients who meet the above eligibility criteria will be approached in primary care when they present with symptoms of chronic breathlessness. An electronic template on the patient record, triggered at the point of consultation, will be used to aid opportunistic recruitment (see figure 1). The template will be triggered by either free text or Read codes relating to breathlessness. Limits have been set on the trigger to avoid it appearing for patients who have an existing diagnosis of COPD or HF. The template summarises the study, prompting the GP to ask if the patient gives consent to be contacted by the study team. The GP will select yes or no as appropriate to the patient agreeing to have their contact details sent to the study team.

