### Intervention—structured diagnostic pathway

Patients who attend GP surgeries in the intervention group will undergo a set of investigations within 1 month; body mass index (BMI), spirometry, ECG, chest X-ray, full blood count, N-terminal (NT)-pro hormone brain natriuretic peptide (NT-proBNP) profile, anxiety and depression screening using the Patient Health Questionnaire—4 item (PHQ-4)^27^ and the General Practice Physical Activity Questionnaire.^28^ The GPs and clinicians will be provided with the pathway document to support a structured history, examination and use of the investigations (figure 3). The electronic template will prompt the GP to action these investigations. The pathway will also be provided as a laminated document for each clinician in the intervention practices, with small laminated flash cards of the investigations available on the work station. The pathway will recommend that patients are reviewed, along with their results, within 1 month and appropriate next steps to be taken regarding patient management.

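### Entry at a second presentation is not tied to when the practice started the study, so second-presentation entrants may differ by arm and bias the diagnosis comparison

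*Protocol article*

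**What the plan says.** **Who may enter.** Eligibility criteria for patients states: "Patients will be eligible if they are over 40 years old, experienced breathlessness for over 2 months and are within their first two presentations". The same section adds: "Exclusion criteria are an existing diagnosis for their current symptom of breathlessness". Neither rule is tied to the date on which the practice began the study, and the exclusion has no reference date. The abstract words entry differently: "Eligibility criteria include patients presenting with chronic breathlessness for the first time".

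**When the arm is fixed.** Allocation is by practice, before patients are identified: "The GP practices will be randomised 1:1 and stratified by CCG using Statarand". Identification then happens consultation by consultation: "An electronic template on the patient record, triggered at the point of consultation, will be used to aid opportunistic recruitment". The Recruitment section says breathlessness free text or Read codes fire the template, and the only limits it describes are existing COPD or heart failure.

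**What the arms do.** The Intervention section applies the panel to patients attending intervention practices, without limiting it to those who have consented. It says "The electronic template will prompt the GP to action these investigations" and "The pathway will recommend that patients are reviewed, along with their results, within 1 month". The usual-care template asks only for permission to pass on contact details, and those GPs are directed to the NICE summary. Written consent comes later, at the research visit.

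**What is compared.** Data analysis plans Cox modelling of time to diagnosis and χ² tests of the proportions diagnosed at 3 months and 1 year. Table 1 takes time to diagnosis from the date of symptom presentation but does not say which presentation counts.

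**The concern.** Take a patient who consults after the practice has started but does not enter, for instance because breathlessness has not yet lasted more than 2 months or the template did not fire on the record. In an intervention practice the panel may still be run. If it yields a diagnosis, the patient is excluded at the next visit. If it does not, the patient is still within two presentations and can enter with the pathway already delivered. In a usual-care practice nothing in the study prompts investigation between the two visits.

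The allocated arm can therefore influence who is available at a second presentation. Intervention entrants at that point would be enriched for patients whom the pathway did not diagnose. The diagnosis comparisons would then set somewhat different populations side by side. The article says the study will help choose the future trial's primary outcome and judge a realistic difference, so a distorted difference would carry forward. The Box 1 weekly recruitment count, which helps set the number and size of future clusters, could also be affected.

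**Working it through.** The plan states no power, effect size or diagnosis rate, so there is no figure of its own to reproduce. The check is a reading of the rules followed by an illustration on assumed rates.

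**1. Do the rules allow it?** Four conditions are needed, and the text allows each:
- entry at a second presentation (eligibility section);
- loss of eligibility on diagnosis (same section);
- delivery of the pathway to people who have not consented (Intervention section);
- a difference between arms in what the template prompts (Intervention section).

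Nothing in the article requires that a second-presentation entrant be untested, or that the first presentation came before the practice started. A patient whose first presentation did precede the start has not had the pathway and is unaffected.

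**2. Assumed inputs.**
- m: share of otherwise eligible patients not captured at their first consultation after the start who return a second time; 0.1 to 0.5.
- d: probability of diagnosis between the two visits; usual care 0.10; intervention 0.1, 0.2, 0.4 or 0.6.
- p: true proportion diagnosed within 3 months of the first consultation; 0.65 intervention and 0.35 usual care, so the true difference is 0.300.

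Missed patients are taken to share the p of the rest, and all who remain eligible are taken to enter.

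**3. Formulas.**
- Share ever available for enrolment = 1 − m·d.
- Observed proportion diagnosed = (p − m·d)/(1 − m·d).

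Worked case, m = 0.5 and intervention d = 0.6:
- intervention pool 1 − 0.30 = 0.70; usual-care pool 1 − 0.05 = 0.95; ratio 0.70/0.95 = 0.737;
- observed proportions (0.65 − 0.30)/0.70 = 0.500 and (0.35 − 0.05)/0.95 = 0.316; difference 0.184.

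**4. Results (usual-care d = 0.10).**

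| Intervention d | Pool ratio, m = 0.1 / 0.3 / 0.5 | Observed difference, m = 0.1 / 0.3 / 0.5 |
|---|---|---|
| 0.1 | 1.000 / 1.000 / 1.000 | 0.303 / 0.309 / 0.316 |
| 0.2 | 0.990 / 0.969 / 0.947 | 0.299 / 0.298 / 0.295 |
| 0.4 | 0.970 / 0.907 / 0.842 | 0.292 / 0.272 / 0.247 |
| 0.6 | 0.949 / 0.845 / 0.737 | 0.284 / 0.243 / 0.184 |

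**5. Direction.** The observed proportion can be rewritten as 1 − (1 − p)/(1 − m·d). For small m, the difference therefore shifts by about −m(0.35·d_int − 0.65·d_uc). With d_uc = 0.10 this is zero at d_int = 0.65 × 0.10/0.35 = 0.186. Above that the difference is understated; below it, slightly overstated, as the first row shows. Unequal pools need only m > 0 and different d. Bias against the intervention needs the pathway to be clearly faster, which is the trial's own hypothesis.

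**6. Time origin.** The formulas count from the first consultation. If time is counted from the second, the pathway has run before time zero for these entrants and its diagnoses are already lost. Choosing an origin does not by itself repair the comparison.

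**7. After restriction.** With first-since-start entrants only, m = 0: both pools are 1.000 and the difference returns to 0.300, provided that the reasons for being missed at the first visit do not depend on arm.

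**The case against.** The strongest reply is that the route is narrow and the stakes are modest. Most patients may be captured at their first visit, the analysis is exploratory, and no power claim depends on it. The article already has the presentation date and the timing of investigations taken from records, so affected entrants could be identified. All of this stands, and it limits the point to a cheap improvement.

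Several stronger readings are tempting but unsupported:
- **That the results review is itself a second presentation.** The article does not say so. An ordinary return visit is enough for the mechanism.
- **That every patient with short-lived symptoms receives the panel.** Whether the prompt precedes the eligibility check depends on figures not available here.
- **That patients who decline contact are offered entry again.** No section describes this. They were eligible when they declined, so they stay in the denominator of the recruitment proportion.
- **That usual-care patients return largely uninvestigated.** Their GPs are directed to the NICE summary, which the Introduction says recommends all these tests. Only the absence of a study prompt is documented.
- **That the recruitment proportion is lowered.** Outcomes defines it as consented over eligible. A patient who never becomes eligible leaves both parts. Only the weekly count could fall, and even there the pathway's return contacts might add recruiting opportunities.

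The abstract's wording does not settle the matter. If first-presentation entry governed, the problem would not arise, but the detailed eligibility section says otherwise.

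**Conclusion.** The point holds as a possible arm-dependent selection that the rules leave open, with no demonstrated size. It can bias time to diagnosis and the 3-month and 1-year proportions, and it can affect the weekly recruitment count. With the pathway at least twice as likely as usual care to give a diagnosis between visits, the illustration ranges from negligible (0.299 against 0.300) to material (0.184). Every rate in it is an assumption, and where the truth lies cannot be read from the article. A reader might infer that the intervention is certain to look worse or that recruitment will be visibly depressed. Neither follows: both depend on how many patients are missed at the first visit, and the first also depends on how much faster the pathway diagnoses. This is worth correcting because the correction is cheap, not because the harm is shown to be large.

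**What to change.** 1. Using the healthcare records already reviewed at 3 and 12 months, record whether the index consultation was the patient's first for breathlessness since the practice started the study.
2. Report recruitment by arm and presentation number.
3. Base the between-arm comparison of time to diagnosis and of the diagnosis proportions, or a stated sensitivity analysis, on patients who entered at their first consultation since practice start, counting time from that consultation.
4. Reconcile the abstract's entry wording with the eligibility section.

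The cost is one extra item from records already being read, and some loss of precision in the diagnosis comparison. Restricting eligibility itself to the first consultation since practice start is optional. It would also remove the problem, but it would reduce recruitment in a study whose primary outcome is recruitment.

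One limit remains. Telephone screening and consent follow the consultation, and the diagnosis exclusion has no reference date, so some arm-dependent loss between consultation and enrolment could persist after this change.

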#### Eligibility criteria for GP practices

GP practices will be approached to take part in this study if they serve a patient population over 10 000. Practices that are research active, as identified by the local Clinical Research Network research scheme, will be approached. The practices will be visited by the study team to discuss taking part in the study and engage with the practice teams.

The GP practices will be randomised 1:1 and stratified by CCG using Statarand,^25^ a Stata randomisation module (Boston College Department of Economics).

#### Recruitment

Patients will be recruited over 1 year. Patients who meet the above eligibility criteria will be approached in primary care when they present with symptoms of chronic breathlessness. An electronic template on the patient record, triggered at the point of consultation, will be used to aid opportunistic recruitment (see figure 1). The template will be triggered by either free text or Read codes relating to breathlessness. Limits have been set on the trigger to avoid it appearing for patients who have an existing diagnosis of COPD or HF. The template summarises the study, prompting the GP to ask if the patient gives consent to be contacted by the study team. The GP will select yes or no as appropriate to the patient agreeing to have their contact details sent to the study team.

**Figure 1 F1:**
[figure not shown]
The electronic template triggered on patient electronic healthcare record. GP, general practitioner.

The electronic template has been developed in partnership with Keele Clinical Trials Unit who will support implementation onto the electronic patient record system (SystmOne and EMIS) for each practice. This approach has been used successfully in other primary care trials.^26^ The Leicester City CCG who take the research lead for Leicester and Leicestershire were consulted regarding the use of the electronic template.

#### Setting

The GP practices are located in Leicester and Leicestershire, England, UK. The research team is based at Glenfield Hospital, University Hospitals of Leicester NHS Trust. Participants will be invited to attend Glenfield Hospital for a research visit.

#### Safety reporting

Participation is considered to be low risk. It is believed the occurrence of any serious adverse events (SAEs) will be low. Participants will be undertaking some physical tests as part of the research. There may be a small risk of worsening breathlessness, changes in blood pressure and changes in heart rate and a very small risk of falls. Trained staff and emergency equipment will be available to deal with any serious events. All adverse events and SAEs will be recorded on the adverse event log. Any SAEs related to the physical tests conducted as part of the study will be reported.

#### Procedure

A weekly search will be performed by practice staff to provide a report of patients who have agreed to be contacted by the study team following discussion with the GP, as described above. The report will be sent via secure encrypted nhs.net email and patients will be contacted to complete telephone screening for eligibility. A script for telephone screening will be available for use to confirm patients’ age, previous medical history and to explain the study in more detail. If patients agree to hear more about the study they will be sent a participant information sheet by post and, where willing, a provisional appointment letter. When patients attend their research visit, they will complete written informed consent (online supplemental file 1) and their GP will be notified of their involvement in the study. For patients who decline to take part in the study or are ineligible, the reasons will be documented and collated.

10.1136/bmjopen-2021-057362.supp1Supplementary data

Where possible, patients will attend their research visit within 1 month of seeing the GP with their breathlessness symptoms. Patients will attend a second research visit 12 months after their initial appointment and also be contacted by phone at 6 months and asked to complete the questionnaire pack, which will be sent in the post. Please see figure 2 for the study schedule.

**Figure 2 F2:**
[figure not shown]
Study schedule. GP, general practitioner; HRQoL, health-related quality of life.

### Intervention—structured diagnostic pathway

Patients who attend GP surgeries in the intervention group will undergo a set of investigations within 1 month; body mass index (BMI), spirometry, ECG, chest X-ray, full blood count, N-terminal (NT)-pro hormone brain natriuretic peptide (NT-proBNP) profile, anxiety and depression screening using the Patient Health Questionnaire—4 item (PHQ-4)^27^ and the General Practice Physical Activity Questionnaire.^28^ The GPs and clinicians will be provided with the pathway document to support a structured history, examination and use of the investigations (figure 3). The electronic template will prompt the GP to action these investigations. The pathway will also be provided as a laminated document for each clinician in the intervention practices, with small laminated flash cards of the investigations available on the work station. The pathway will recommend that patients are reviewed, along with their results, within 1 month and appropriate next steps to be taken regarding patient management.

**Figure 3 F3:**
[figure not shown]
Diagnostic pathway. BNP, brain natriuretic peptide; BP, blood pressure; COPD, chronic obstructive pulmonary disease; FBC, full blood count; FEV1, forced expiratory volume in 1 s; FVC, forced vital capacity; GPPAQ, General Practice Physical Activity Questionnaire; HR, heart rate; JVP, jugular venous pressure; MRC, Medical Research Council; PHQ-4, Patient Health Questionnaire 4; PND, paroxysmal nocturnal dyspnoea; PRISM, Patient and Referral Implementation SysteM; RR, respiratory rate; TSH, thyroid stimulating hormone.

Usual care will also have the electronic template triggered but will only ask the patient for their consent to pass on contact details to the study team. The GPs and clinicians in usual care will be asked to proceed with investigating the patient and their symptoms as per their usual practice and be directed to the NICE Clinical Knowledge summary for breathlessness^14^ to standardise care.

### Outcomes

As this is a feasibility trial, a formal sample size/power calculation is not required. Recruitment itself is one of the main measures of feasibility. The feasibility measures are outlined in box 1 and the secondary outcome measures in table 1. Recruitment rate will be recorded as a proportion of participants consented compared with the number of participants identified as eligible by the GP practices.

### Data collection

Data will be collected in accordance with sponsor policies and standard operating procedures. Baseline data will be collected at research visit 1, within 1 month of the patient consulting their GP for breathlessness. Questionnaires will be completed by post at 6 months and visit 2 will occur at 12 months after visit 1. Healthcare records will be reviewed for all patients at 3 and 12 months to record the investigations performed and when, diagnosis and time to diagnosis.

Detailed healthcare utilisation data will be recorded at 12 months and 5 years, including hospital admissions, healthcare use and patient survival. This information will be collected from GP records and NHS digital.

### Anthropometric measures

BMI will be calculated by measuring the patient’s height and weight. Body composition using bioelectrical impedance will provide measurements of lean mass and body fat percentage. Each participant’s waist and hip circumference will be measured to the nearest 0.1 cm.

### Patient-reported outcome measures

#### HRQoL

The Chronic Heart Questionnaire Self-Report is a validated and responsive questionnaire developed for patients with heart disease to assess HRQoL.^29^ It has four domains: dyspnoea, fatigue, mastery and emotional function and a known minimal clinically important difference in patients with chronic heart and lung disease (Chronic Respiratory Questionnaire version). We will be using it in a population with undifferentiated breathlessness as part of feasibility.

The EuroQol 5 Dimension 5 Level questionnaire (EQ5D-5L)^30^ will be used to assess generic HRQoL. The EQ5D-5L was chosen as it is a standardised measure of health status independent of disease used to calculate quality-adjusted life years (QALY).

